## Abstract

**Background:**

Individuals with a family history of cancer face an increased risk of developing breast and ovarian cancer. Up to 30% of the 70,000 annual breast cancer cases in Germany are associated with a familial cancer burden. Early identification of these risks is crucial as personalised measures can enable early detection or prevention of cancer. Primary care gynaecologists are uniquely suited to assess family histories and facilitate referrals to hereditary cancer centres. However, solutions on how to support early referral are still lacking. This study evaluates the impact of the digital care platform dVP_FAM as a potential remedy compared to standard care. The primary hypothesis is that the platform will increase the proportion of care-seeking women with a familial cancer risk who have not yet developed cancer. Secondary outcomes include improvements in care efficiency, patient empowerment, and health-related quality of life.

**Methods:**

The study is a multi-centre, cluster-randomised, mixed-method trial involving 44 gynaecological centres and 800 participants recruited through hereditary breast and ovarian cancer centres. All participants receive standard guideline-based care, while the intervention group also uses the dVP_FAM platform. The primary endpoint measures the proportion of participants with a familial cancer history who are cancer-free when seeking specialist counselling. Secondary outcomes are assessed using validated tools like the SF-12 and custom measures. Data collection employs a convergent mixed-methods approach, integrating quantitative and qualitative evidence.

**Discussion:**

The dVP_FAM platform represents an innovative approach to digitising cancer prevention in Germany, enhancing early detection and care coordination. If successful, dVP_FAM could serve as a scalable model for digital health innovations, improving efficiency and modernising the delivery of personalised care across health systems.

**Trial registration:**

German Clinical Trials Register, DRKS00030371. Registered on 02 October 2023.

**Supplementary Information:**

The online version contains supplementary material available at 10.1186/s13063-025-08872-0.

## Introduction

### Background and rationale {6a}

In recent years, advances in personalised medicine have highlighted the role of genetic factors in cancer, both for diagnosis and for tailoring treatment. The rapidly expanding knowledge in this area has the potential to benefit an increasing number of cancer patients and, importantly, also healthy individuals who seek advice because a family history may increase their own risk of developing cancer [1]. Up to 30% of the 70,000 patients, who are newly diagnosed with breast cancer each year in Germany, present with a familial cancer burden [2–4]. If a pathogenic variant is identified in these patients, they may benefit from personalised treatment and/or secondary and tertiary prevention [5]. For individuals with a family history of cancer who have not yet developed the disease (“healthy sick”), there are now not only early detection measures but also prophylactic measures available that can ideally prevent the development of breast or ovarian cancer. To achieve this individualised approach, patients (“healthy sick” and already diseased) and their physicians must be able to accurately assess the risk [6, 7].

Primary care gynaecologists play a key role in this process. By routinely assessing a patient’s family cancer history, they could identify at-risk but healthy women, ideally before cancer develops [8–10]. To date, there has been no standardised integration of early risk assessment through primary care physicians into the specialised care of the hereditary breast and ovarian cancer centres (HBOC-centres) in Germany. Studies [7, 11–13] have shown that not all primary care gynaecologists have the necessary knowledge to routinely perform an initial risk assessment as part of taking the family history and, if necessary, refer patients to a specialised HBOC-centre. Knowledge about family history as a risk factor is essential, however, for physicians to take early action and to help those affected to benefit as fully as possible from available prevention and treatment options.

Digital technologies have the potential to facilitate screening processes for patients and health professionals, simplify referrals to specialised counselling centres for patients at risk, and support cross-sectoral information exchange between providers, thereby enabling earlier and more effective identification of individuals with a familial cancer risk [14, 15]. Ultimately, this may increase the proportion of healthy individuals benefitting from the available prevention and treatment options. This study protocol describes the development of a transsectoral digital care platform for individuals with familial cancer risk and its evaluation in a multi-centre, cluster-randomised, mixed-methods study.

### Objectives {7}

The aim of the study is to investigate if and how individuals with a family history of cancer risk benefit from using the newly developed digital care platform (dVP_FAM) as opposed to individuals with a family history of cancer risk who are provided with standard care. The digital platform is intended to identify more individuals with familial cancer risks at an early stage, before they develop cancer (primary endpoint). Furthermore, we expect improvements regarding the efficiency of care, patient empowerment, and health-related quality of life (secondary endpoints).

#### Primary hypothesis

(H1): In the intervention group (IG), the proportion of patients with a family history of cancer not diagnosed with breast or ovarian cancer to patients diagnosed with breast or ovarian cancer is higher than in the control group (CG).

#### Secondary hypotheses

(H2): After 9 months, there is an improvement in the transsectoral exchange of information and care efficiency in the IG compared to the CG.

(H3): After 9 months, patients in the IG report an increased sense of empowerment and a better health-related quality of life than patients in the CG.

### Trial design {8}

The trial is designed as a two-arm multicentre, cluster-randomised mixed-methods study. The convergent design is used as the mixed-method design method. The mixed-methods approach combines qualitative and quantitative methods in a single research design [16]. In this way, the weaknesses of the two methodological approaches (quantitative and qualitative) can be balanced out. The design of our study is intended to quantify the effect of the dVP_FAM compared to standard care and at the same time to provide a deeper understanding of the effects of the digital intervention on the everyday practice of patients and health care providers. The quantitative methods should meet the requirements of theory- and hypothesis-driven research as well as the statistical generalisability of findings [16], which requires the recruitment of a large sample. In addition, we use a qualitative approach, which is intended to capture more in-depth patterns [16]. The qualitative part is more open-ended and less hypothesis-driven than the quantitative part. Individual cases will be described in as much detail as possible. Both approaches thus form a field of tension between standardisation and methodological openness and flexibility. In our project, the methodology is complementary in order to obtain a comprehensive picture of the primary and secondary endpoints. The intervention starts at the primary gynaecological care level by screening for familial risk of breast and/or ovarian cancer using the digital platform in the intervention arm. If a patient meets the inclusion criteria for a familial risk of breast and/or ovarian cancer, the physicians in the study centre can recommend an appointment for specialised care and counselling in a HBOC-centre via the digital platform. In the control arm, referrals will be made according to standard practice. The primary endpoint is the quantitative one-time assessment of the proportion of individuals with a family history of cancer who are not diagnosed with cancer when presenting at specialised counselling compared to those with a family history of cancer already diagnosed with cancer. It is assumed that the treatment group demonstrates superiority over the control group. All women who are assessed for the primary endpoint are additionally asked whether they would like to participate in the longitudinal study. The secondary endpoints, transsectoral information exchange, care efficiency, quality of life and patient empowerment, are assessed as follows: (1) a longitudinal study will be conducted at three measurement points (baseline, after 3 months, after 9 months), (2) semi-structured interviews with patients, physicians and medical assistants, and (3) field observations. In addition, a multidisciplinary team will analyse the ethical, legal and psychosocial (ELSI) implications of the development and use of the dVP_FAM throughout the project.

## Methods: participants, interventions, and outcomes

### Study setting {9}

The study is coordinated by the Department of Anesthesiology and Intensive Care Medicine of Charité – Universitätsmedizin Berlin. All participants will be recruited at the HBOC-centres of Charité – Universitätsmedizin Berlin (Charité) and the University Medicine Greifswald (UM Greifswald) (recruiting institutions). The statistical analysis is carried out after completion of the data collection at the Institute of Biometry and Clinical Epidemiology (iBikE) of Charité – Universitätsmedizin Berlin (data evaluation institution).

### Eligibility criteria {10}

Inclusion criteria for participating study centres (primary care gynaecologists, breast and gynaecological cancer centres):▪ Access to a computer with WiFi

Exclusion criteria for participating study centres:▪ Study centre located outside of Berlin, Brandenburg, and Mecklenburg-Vorpommern

Inclusion criteria for participating patients (longitudinal study):▪ All patients must meet the inclusion criteria for a specialised counselling at a HBOC-centre, which are based on a checklist developed by the German Cancer Society (DKG) [17]▪ Patients who were treated in one of the participating study centres▪ Aged ≥ 18 to 80▪ Access to a computer/tablet/smartphone with WiFi▪ Written consent obtained

Exclusion criteria for participating patients (longitudinal study):▪ Insufficient German language ability▪ Severe psychological distress

### Who will take informed consent? {26a}

Recruiting institutions (HBOC-centres) will obtain written informed consent from potential trial participants after they have been informed about the study and are willing to participate. Informed consent will be obtained from all study centres and study participants.

### Additional consent provisions for collection and use of participant data and biological specimens {26b}

The consent form will also ask participants to agree that, if they withdraw from the study, their data collected up to that point may be processed. No other terms of consent will be requested.

## Interventions

### Explanation for the choice of comparators {6b}

The care of individuals with a familial risk of breast and ovarian cancer in IG and CG is guideline-based according to the German Consortium for Hereditary Breast and Ovarian Cancer (GC-HBOC). The non-digital approach to identifying a familial cancer risk is used as the comparator.

### Intervention description {11a}

In the IG, the digital care platform dVP_FAM is used to provide guideline-based specialist care for individuals with familial cancer risk. The digital platform consists of several components [18].

In a first step, the study centres collect the family history using a digital questionnaire integrated in the dVP_FAM, which digitally implements a checklist validated and endorsed by the DKG for recording a possible familial risk of breast and/or ovarian cancer [4, 17]. If a patient meets the inclusion criteria for a familial risk of breast and/or ovarian cancer, the physicians in the study centre can recommend an appointment for specialised care and counselling in a HBOC-centre via the digital platform.

For this purpose, the physicians in the study centres invite their patients to activate a personalised platform account, which they can use to (1) request an appointment in the HBOC-centre; (2) access evidence-based and easy-to-understand information on familial breast and ovarian cancer and related risk management options; and (3) find information about psychosocial support. Once scheduled, the 60-min specialist counselling at the HBOC-centre is supported by the digital care platform via visualisations and other information resources. Following the consultation, patients may re-access the platform at any time to obtain further information or get in touch with their counselling centre. Similar to an electronic patient record, patients and their physicians can also use the platform to save medical findings and reports and share them with other physicians involved in their care. The latter is the basis of our thesis of an improved exchange of information between patients and health care providers.

### Criteria for discontinuing or modifying allocated interventions {11b}

In principle, participating in the study should not constitute a physical risk. However, it cannot be completely ruled out that emotional stress may increase during participation. For this reason, participants are explicitly informed at each measurement point that they can end their participation at any time and without giving reasons or having any negative consequences. Furthermore, the study participants are given access to a psychologically trained contact person to whom they can turn if needed. A sensitive verbal and written consent procedure ensures that participation is voluntary. Part of the consent procedure is a detailed explanation of the study and the provision of study materials (study information, flyer, and reference to the homepage: www.dvp-fam.de). In order to standardise the procedure in the study centres as far as possible, we will provide comprehensive information material. If study participants withdraw their consent, no further data will be collected. However, the data processing carried out until the withdrawal remains lawful. In the event of withdrawal, participants may also request the deletion of their data.

### Strategies to improve adherence to interventions {11c}

The study is subject to careful monitoring regarding conditions in the study centres, proper conduct, recruitment and handling of adverse events. To ensure the same conditions for all study participants, whether under intervention or control condition, all of the study staff are trained according to a defined two-step procedure and standard operating procedures for all steps involved. The training first starts with an outline of the study procedure, from the time of recruitment of individual study centres to initial patient contact to completion of their participation in the study. Second, as part of the training, the physicians in the study centres and in the HBOC-centres are instructed on how to use the platform.

### Relevant concomitant care permitted or prohibited during the trial {11 d}

Not applicable. No concomitant care or interventions are planned. No concomitant care or interventions are explicitly prohibited.

### Provisions for post-trial care {30}

Medical advice and care will continue to be provided by the respective study centre regardless of participation in the study.

### Outcomes {12}

Table 1 lists the primary and secondary outcomes and covariates along with the measurement instruments used in the quantitative questionnaire study. The primary endpoint is determined after specialised counselling in the HBOC-centre, while the secondary endpoints are assessed at *t*2 (at 9 months after baseline).

**Table 1 Tab1:** Quantitative primary and secondary outcome measures and additional variables

Domain	Measure	Metric	Source of data	Time points^a^		
				*t*0	*t*1	*t*2
**Primary outcome**						
Percentage of patients not diagnosed with breast or ovarian cancer seeking specialised advice	Descriptive items	Descriptive methods^b^	Monitoring	x		
**Secondary outcome**						
Transsectoral information exchange and care efficiency	Descriptive items	Descriptive methods	Self-report-questionnaires: patients	x	x	x
	Descriptive items	Descriptive methods	Self-report-questionnaires: medical staff HBOC-centre	x		
Patient empowerment	Genetic Counseling Outcome Scale [19]	Descriptive methods based on sum score	Self-report-questionnaires: patients	x	x	x
Quality of life	Short-Form-Health-Survey-12 [20–22]	Descriptive methods based on sum score	Self-report-questionnaires: patients	x	x	x
**Additional variables**						
Demographics	Descriptive items	Descriptive methods	Self-report-questionnaires: patients	x		
Clinical variables	Descriptive Items	Descriptive methods	Self-report-questionnaires: patients	x		x
Risk perception	Subjective risk perception [23]	Descriptive methods based on sum score	Self-report-questionnaires: patients	x	x	x
Decision-making behaviour	Decisional Conflict Scale [24, 25]; Decision Regret Scale [26]	Descriptive methods based on sum score	Self-report-questionnaires: patients	x		x
Technical affinity	Affinity for Technology Interaction Scale [27]	Descriptive methods based on sum score	Self-report-questionnaires: patients	x		
User behaviour dVP_FAM	Descriptive items	Descriptive methods	Self-report-questionnaires: patients	x	x	x

^a^
*t*0: baseline; *t*1: 3 months; *t*2: 9 months

^b^ See section descriptive methods {20}

#### Primary outcome measure

The primary endpoint is the percentage of individuals with a family history of cancer who are not diagnosed with breast or ovarian cancer compared to those diagnosed with these types of cancer. This outcome will be assessed once patients from a study centre (IG or CG condition) register and receive counselling at one of the specialised HBOC-centres (see Table 1).

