**Fig. 2 Fig2:**
[figure not shown]
Flowchart of the second study phase: recruitment at the HBOC-centres

All patients attending the HBOC-centre referred by a study centre under intervention or control conditions are monitored. Patients with familial cancer risk according to the DKG-checklist are included in the analysis of the primary endpoint.

i. Recruitment for the longitudinal questionnaire study (see Fig. 2)

Patients who present at the specialised HBOC-centre after screening and agree to participate in the study complete a self-report questionnaire at three measurement points (*t*0: baseline; *t*1: 3 months; *t*2: 9 months). The baseline measurement t0 takes place after the initial counselling with a specialised physician in the HBOC-centre. Study participants receive an e-mail link to the online questionnaire after the counselling. Three and 9 months after the initial counselling, the study participants receive further online questionnaires for *t*1 and *t*2 via e-mail.

ii. Survey of medical staff at the HBOC-centre (see Fig. 2)

At the HBOC-centre, medical staff record all services performed before and after counselling on an individual patient basis using a self-report questionnaire. This allows to compare the efficiency of care under intervention and control conditions from a provider’s perspective.

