### Methods for additional analyses (e.g. subgroup analyses) {20b}

No additional analyses will be performed.

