## Discussion

This is a multicentred, cluster-randomised study in a mixed-methods design (a quantitative and a qualitative part). The study investigates whether and to what extent individuals with a family history of cancer benefit from using the digital care platform (dVP_FAM) compared to those receiving standard care. The dVP_FAM aims to identify individuals with a familial cancer risk earlier—ideally before they develop cancer. In our study, this success would be reflected by an increase in the identification of individuals with a family history of cancer who have not yet developed the disease (primary endpoint). The study also assesses potential improvements in care efficiency, patient empowerment and health-related quality of life (secondary endpoints).

Digital technologies can bring the dynamic growth of knowledge in medicine, particularly in the field of familial cancer, from cutting-edge medicine to the general public [7, 14, 40]. If we can show that dVP_FAM helps to identify individuals with a familial cancer risk earlier, this innovative approach contributes to improving specialised, personalised care and cancer prevention and can act as a driving force for the health system-wide digitalisation in Germany and beyond. However, it must be noted that the implementation risks include (1) reservations about digital innovations, (2) a lack of human resources and (3) a low level of digital literacy. Overall, digitalisation in Germany is lagging behind international developments [41].

The development of digital technologies raises not only technical but also ethical and legal questions. The transdisciplinary perspective involving patient representatives is essential for their development and evaluation. The active involvement of patient representatives in the development of the intervention, the evaluation and the interpretation of the results can therefore be regarded as one of the strengths of our study. The “ELSI” track accompanies the entire process and contributes the perspectives of physicians, psychologists, patients, legal scholars, biometricians and medical ethicists. The complex mixed-methods design is also due to our multidisciplinary concept: the different methodological approaches not only compensate for the weaknesses of the respectively other approach but also enable a more comprehensive understanding of the research problem.

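### The primary endpoint compares the mix of women reaching the HBOC-centres, but the objective and discussion read it as more cancer-free women identified, and no between-arm comparison of numbers is planned

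*Protocol article*

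**What the plan says.** The Primary outcome measure section states: "The primary endpoint is the percentage of individuals with a family history of cancer who are not diagnosed with breast or ovarian cancer". It is assessed once women from a study centre "register and receive counselling at one of the specialised HBOC-centres". The Participant timeline fixes the analysis set: "Patients with familial cancer risk according to the DKG-checklist are included in the analysis of the primary endpoint". The Primary endpoint analysis compares this percentage between arms by logistic regression with a random intercept per study centre and tests OR = 1. H1, the abstract, Table 1 and the Sample size section are all worded as a proportion and agree with that analysis.

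Two places read the endpoint differently. The Objectives say "The digital platform is intended to identify more individuals with familial cancer risks at an early stage, before they develop cancer" and label this aim, in brackets, as the primary endpoint. The Discussion says "this success would be reflected by an increase in the identification of individuals with a family history of cancer" who are still free of the disease. Both speak of how many women are identified.

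On counts, the Descriptive methods section reports absolute as well as relative frequencies for categorical data. Table 1 lists no count or rate as an outcome, and section {20b} states "No additional analyses will be performed".

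**The concern.** The denominator consists of women who were screened, referred, booked and then attended. In the intervention arm the platform acts on screening, referral and booking; in the control arm women follow the usual pathway (Participant timeline {13}). Randomising centres makes the centres comparable. It does not make the women who attend comparable, because the intervention helps to decide who attends.

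A share has two components, and either can move it. Breast and gynaecological cancer centres are among the study centres (Recruitment {15}), so systematic family-history taking could plausibly bring in more women who already have a diagnosis as well as more who do not. The platform could then identify many more cancer-free women and H1 would show little or nothing. Conversely, a positive H1 does not by itself say that the number of cancer-free women rose. At stake is the trial's headline sentence, not the validity of the test of H1.

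**Working it through.** **Inputs** (Sample size {14}): 20 centres per arm after dropout, an average of 20 participants per centre in both arms, 60% cancer-free in control and 70% under intervention, ICC 0.01, two-sided alpha 0.05, unpooled Z-test, power about 80%.

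**The plan's own figure.** Design effect = 1 + (20 − 1) × 0.01 = 1.19. Effective n per arm = 400 / 1.19 = 336.1. Standard error = √[(0.7 × 0.3 + 0.6 × 0.4) / 336.1] = 0.0366. Power = Φ(0.10 / 0.0366 − 1.96) = 0.78. This agrees with about 80%, so the sample-size arithmetic is not in question.

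**What the odds ratio measures.** Let H be cancer-free attenders and C attenders with cancer, per centre. The share is H / (H + C). With equal numbers of centres per arm and equal recruitment time, the crude odds ratio is (H₁/C₁) / (H₀/C₀) = (H₁/H₀) / (C₁/C₀). It is the rate ratio for cancer-free women divided by the rate ratio for women with cancer. H1 tests this quotient and cannot separate its two parts.

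**Scenarios.** The control centre follows from the plan: 20 × 0.60 = 12 cancer-free and 8 with cancer. The planned OR is (0.7/0.3) / (0.6/0.4) = 1.56. Apart from the equal-size row, the intervention counts are illustrative assumptions.

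| Intervention centre (H + C) | Share | OR | Cancer-free women vs 12 |
|---|---|---|---|
| 14 + 6 (equal size, as the plan assumes) | 70% | 1.56 | +17% |
| 18.7 + 8 (8 × 0.7/0.3 = 18.7) | 70% | 1.56 | +56% |
| 12 + 5.1 (12 × 0.3/0.7 = 5.14) | 70% | 1.56 | 0% |
| 10.5 + 4.5 | 70% | 1.56 | −12.5% |
| 24 + 16 | 60% | 1.00 | +100% |
| 18 + 16 | 52.9% | 0.75 | +50% |

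The first four rows give the same primary result with different changes in the number identified. The last two give a null or adverse result although more cancer-free women were identified.

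**Precision of a direct count comparison.** At the plan's equal-size case, 14 versus 12 per centre with 20 centres per arm, log rate ratio = ln(14/12) = 0.154. Without overdispersion the variance is 1/280 + 1/240 = 0.00774 and the standard error 0.088. Power = Φ(0.154/0.088 − 1.96) = Φ(−0.21) = 0.42. With a negative-binomial dispersion of 0.1 the variance is [(1/14 + 0.1) + (1/12 + 0.1)] / 20 = 0.0177, the standard error 0.133 and power about 21%. At 0.3 it is about 12%. The documents give no dispersion; these two values are assumptions.

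**The case against.** The case on the other side has real weight.

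- **The operative plan is coherent.** H1, the abstract, the endpoint, the sample size and the analysis all use a proportion. The Discussion also speaks of identifying women earlier, and the share still cancer-free at presentation is a defensible measure of that. This stands: the mismatch is with the wording in the Objectives and Discussion.
- **Counts will be visible.** A reader might infer from section {20b} that the numbers of cancer-free women will go unreported. The documents do not support this, since absolute frequencies are to be described. What is absent is a between-arm estimate with its uncertainty, allowing for clustering, recruitment time and centre size.
- **At equal cluster size, 70% does mean more cancer-free women** (14 versus 12). This stands under that assumption. But an average of 20 per centre in each arm is a planning assumption, and the intervention is meant to act on referral.
- **Fewer referrals of women with cancer has no stated mechanism.** A reader might infer that a positive H1 would probably reflect such a fall. Nothing in the documents suggests that the platform deters these referrals. The 12 + 5.1 row shows only what the endpoint cannot exclude; 24 + 16 is the more plausible difficulty.
- **Counts carry their own bias.** Control women are recognised at the HBOC-centre by a study reference on the referral form. Missing references would lower control counts and inflate a rate ratio, whereas the share is unaffected if omission is unrelated to cancer status. This stands and limits how a count analysis can be used.

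**Conclusion.** The point holds as one of interpretation plus a missing supportive estimate. The test of H1 is sound for what it tests: the mix of attenders. It does not establish the increase in identification that the Objectives and Discussion attach to it. The planned OR of 1.56 is compatible with changes in cancer-free attenders from −12.5% to +56% in the scenarios shown, and a doubling is compatible with OR = 1. The algebra is exact; the scenario counts are illustrative.

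A reader might go further and conclude that the endpoint is invalid, or that any claim of more women identified should require a significant rate ratio. Neither follows. The endpoint matches H1, and with about 42% power at best in the plan's equal-size case, such a requirement would usually fail in a trial that achieved its planned effect. This is an inexpensive improvement that changes what the trial can properly conclude.

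**What to change.** Keep H1, its test, alpha and sample size. Before database closure:

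1. In the Objectives, the Discussion and the results report, limit the conclusion from H1 to a change in the share of attenders who are cancer-free at presentation.
2. Amend section {20b} to add one pre-specified supportive analysis: the between-arm rate ratio, with 95% CI, of cancer-free checklist-positive attenders per centre and, separately, of such attenders with cancer. Use a count model that allows overdispersion, such as negative binomial. Include centres with zero attenders, take log recruitment time as offset, and use the strata and centre size as covariates. Enter size within centre type, because practices are measured in billing slips and cancer centres in patients. The period for cancer-centre size (year or quarter) is stated inconsistently in section {16a} and must be reconciled first.
3. State that this analysis shows which component moved the share and is not a significance gate on H1.
4. Check and report how completely control attenders were recognised from the referral-form reference.

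The cost is one extra model specification, fitted once to each count. The HBOC-centres already monitor all attenders referred by study centres, and centre size was collected for stratification. The drawbacks are low precision, as shown above, and possible under-counting of control attenders, which the check in step 4 may reveal but cannot fully repair.
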